## Abstract

**Background:**

Sepsis remains a major health challenge with high mortality. Adequate volume administration is fundamental for a successful outcome. However, individual fluid needs differ between patients due to varying degrees of systemic vasodilation, circulatory flow maldistribution, and increased vascular permeability. The current fluid resuscitation practice has been questioned. Fluid overload is associated with higher mortality in sepsis. A sign of fluid overload is extravascular lung water, seen as B lines in lung ultrasound. B lines correlate inversely with oxygenation (measured by a ratio of the partial pressure of arterial oxygen to the fraction of inspired oxygen ie, PaO2/FiO2). Thus, B lines seen by bedside ultrasound may have a role in guiding fluid therapy.

**Objective:**

We aim to evaluate if fluid administration guided by lung ultrasound in patients with sepsis in emergency departments will lead to better oxygenation and patient outcomes than those in the standard therapy.

**Methods:**

A phase II, multicenter, randomized, open-label, parallel-group, superiority trial will be performed. Patients will be recruited at emergency departments of the participating centers. A total of 340 patients will be randomly allocated to the intervention or standard-of-care group (30mL/kg). The intervention group will receive ultrasound-guided intravenous fluid until 3 B lines appear. The primary outcome will be oxygenation (measured as PaO2/FiO2 ratio) at 48 hours after starting intravenous fluid administration. Secondary outcomes will be patients’ outcome parameters, including oxygenation after 15 mL/kg fluid at 6, 12, 24, and 48 hours; sepsis progress through Sequential Organ Failure Assessment (SOFA) scores; pulmonary edema evaluation; and 30-day mortality.

**Results:**

The trial will be conducted in accordance with the Declaration of Helsinki. Institutional review board approval will be sought after the participating sites are selected. The protocol will be registered once the institutional review board approval is granted. The trial duration is expected to be 1.5-2.5 years. The study is planned to be performed from 2021 to 2022, with enrollment starting in 2021. First results are expected in 2022. Informed written consent will be obtained before the patient’s enrollment in the study. An interim analysis and data monitoring will ensure the patient safety. The results will be published in a peer-reviewed journal and discussed at international conferences.

**Conclusions:**

This is a protocol for a randomized control trial that aims to evaluate the role of bedside ultrasound in guiding fluid therapy in patients with sepsis via B lines evaluation.

**International Registered Report Identifier (IRRID):**

PRR1-10.2196/15997

## Introduction

Sepsis is a significant cause of in-hospital mortality [1]. Prompt and adequate intravenous (IV) fluid therapy is essential in the treatment of sepsis and to reduce sepsis mortality [2,3]. Especially, immediate initial resuscitation in an emergency department can impact patients’ outcomes [4-6]. In 2001, fluid resuscitation with the volume of 30 mL/kg, as early-goal directed-therapy, was added to the standard therapy for sepsis in the emergency department [7]. However, later studies on the Protocolized Care for Early Septic Shock (ProCESS), Australasian Resuscitation in Sepsis Evaluation (ARISE), and Protocolised Management in Sepsis (ProMISe) debated this initial fluid amount. These studies suggested that the fixed amount approach is not appropriate and beneficial for all patients and can be even harmful [8-11]. Even the 2016 definitions of sepsis and septic shock (Sepsis-3) failed to redefine this amount [12-14].

Studies suggest that only 50% of patients with sepsis respond positively to increased fluid administration [15] since the mechanism of circulatory compromise in sepsis is not related to actual hypovolemia. Therefore, excessive volumes are considered harmful and can cause myocardial dysfunction, pulmonary congestion, and decreased cardiac output [16].

Techniques like passive leg raising and inferior vena cava monitoring are useful to identify additional fluid responsiveness in patients [17-19]. However, these tests are cumbersome and time-consuming, especially in the busy emergency department setting [20]. Reliability of passive leg raising test is limited for spontaneously breathing patients or with intra-abdominal hypertension. The test may also be inconvenient in case of pain [18,19,21]. Hence, there is a need for additional means to guide fluid therapy in patients with sepsis.

There is evidence that bedside lung ultrasound can guide the fluid therapy. Positive net fluid balance correlates with extravascular lung water (EVLW) and is associated with higher mortality in patients with sepsis [5]. EVLW detection by the Fluid Administration Limited by Lung Sonography (FALLS)-protocol can be used to monitor acute circulatory failure based on the presence of B lines [22,23]. B lines are related to the thickening of interlobular septa, which is a pathological ultrasound sign [22,24,25]. Additionally, lung ultrasound is used to detect pulmonary edema with a sensitivity and specificity of 97% and 95%, respectively [22,25].

Observational studies suggest that the number of B lines correlates with the amount of EVLW. There is an inverse correlation between the number of B lines and oxygenation measured as the ratio of the partial pressure of arterial oxygen (PaO_2_) to the fraction of inspired oxygen (FiO_2_) [26]. The PaO_2_/FiO_2_ ratio is an integral part of the Sequential Organ Failure Assessment (SOFA) score, a score to assess and diagnose sepsis severity [14,27,28]. Elevated SOFA scores are associated with higher mortality in patients with sepsis [29]. However, lung ultrasound for guiding individualized fluid treatment in sepsis has never been tested in a randomized controlled setting.

We propose to limit the initial fluid volume in the treatment of patients with sepsis in the emergency department by detecting EVLW with lung ultrasound. This approach could enable physicians to better assess and meet individual fluid needs of patients with sepsis. This proposal may also lead to an improved therapy regimen for initial sepsis treatment that avoids administration of excess fluid volume, in turn, limits the consequent damage and decreases mortality in this high-risk group.

Therefore, we plan a randomized controlled trial with the primary objective to assess if fluid administration guided by bedside lung ultrasound can lead to an improved oxygenation (PaO_2_/FiO_2_) 48 hours after fluid administration than that in the current standard of care fluid administration in adult patients with sepsis in the emergency department.

Secondary objectives are to determine whether fluid administration guided by bedside lung ultrasound positively impacts the course of treatment after 15 mL/kg fluid at 0, 6, 12, 24, and 48 hours. These objectives will be evaluated by PaO_2_/FiO_2_ ratio, pulmonary outcomes (pulmonary edema, acute respiratory distress syndrome, or the need for invasive mechanical ventilation), the severity of sepsis (SOFA score), kidney function (mean creatinine level), the volume of administered fluid, and 30-day mortality.

## Methods

### Study Design

The trial (protocol version 1.1, April 2020; preprint version 1.0, April 2019 [30]) will be conducted as a prospective phase II multicenter, open-label with blinded endpoint assessment, parallel-group, randomized controlled trial. Study design will follow the Population, Intervention, Control, Outcome, and Time (PICOT) format (Multimedia Appendices 1 and 2). SPIRIT (Standard Protocol Items: Recommendations for Interventional Trials)- and CONSORT (Consolidated Standards of Reporting Trials)-compliant flow diagram is shown Figure 1.

Multimedia Appendices 2 and 3 respectively present SPIRIT-compliant flow diagram and checklist, respectively.

The schedule of enrollment, interventions and assessments is shown in Table 1.

**Figure 1 figure1:**
[figure not shown]
SPIRIT- and CONSORT-compliant flow diagram of study design. ED: emergency department; FiO2: fraction of inspired oxygen; GCS: Glasgow Coma Scale; IV: intravenous; PaO2: partial pressure of arterial oxygen; qSOFA: quick Sequential Organ Failure Assessment; SOFA: Sequential Organ Failure Assessment; US: ultrasound.

**Table 1 table1:** SPIRIT-compliant schedule of enrollment, interventions and assessments.

Study schedule sections		Study period								
		Enrollment	Allocation	Post-allocation						Prognosis
Time points		T1^a^	0 h	6 h	12 h	24 h	48 h	In-between	30 d	
**Enrollment**										
	Eligibility screening	X								
	Informed consent	X								
	Registration form	X								
	Baseline assessment (clinical features): sepsis with a qSOFA^b^ score≥2; low systolic blood pressure≤100 mmHg; respiratory rate≥22 breaths per minute; altered mentation with Glasgow coma scale score<15		X							
	Baseline assessment (laboratory parameters): ultrasound; PaO_2_/FiO_2_; arterial blood gas analysis; x-ray, NT-proBNP		X							
	Allocation		X							
**Interventions**										
	Intervention arm (fluid administration - 15mL/kg and ultrasound)		X	X	X	X	X			
	Placebo (standard-of-care - 30mL/kg)		X	X	X	X	X			
**Assessments**										
	Primary (PaO_2_/FiO_2_)^c^		X	X	X	X	X			
	Secondary: PaO_2_/FiO_2_/Pulmonary outcome/SOFA^d^ score/creatinine/volume		X	X	X	X	X			
	Prognosis (30-day mortality)								X	
	Documentation (amount of fluid)			X	X	X	X	X		

^a^T1: timepoint 1 before baseline; unknown units of time.

^b^qSOFA: quick Sequential Organ Failure Assessment.

^c^PaO_2_/FiO_2_: partial pressure of arterial oxygen/ fraction of inspired oxygen.

^d^SOFA: Sequential Organ Failure Assessment.

### Study Setting and Study Center Requirements

The study will be conducted as a multicenter study. Centers will be chosen and listed in the trial registration. Inclusion criteria will be as follows: patients with sepsis admission rate≥1000 patients/year; emergency department with necessary resources; personal and technical equipment (chest x-ray, point-of-care ultrasound devices, and access to blood analysis); intensive care unit (ICU); 24-hour availability of trained physicians; and academic hospital with an institutional review board conforming with the main center’s institutional review board). The participating centers will follow standardized written protocols for the evaluation and acute treatment of patients with suspected sepsis or septic shock.

To guarantee compliance with the protocol and application of the same technique, physicians responsible for ultrasound will participate in a practical workshop for lung ultrasound conducted by physicians from the main study center. These participant physicians must demonstrate their competency in lung ultrasounds (through 20 or more scans that will be validated by a main center radiologist or a point-of-care ultrasound–certified emergency department physician).

The physicians responsible for the treatment will have experience in the treatment of patients with sepsis following the hospital's standardized protocols and Sepsis-3 guidelines. Investigators following up on patients will be either physicians or trained nurses.

Adherence to the study requirements and standardized protocol will be ensured at the participating sites with periodic quality monitoring and training of the associated staff.

Further roles and details will be mentioned in the protocol registered after acquiring funding, ethical approval, and selecting participating centers [31].

### Recruitment and Adherence

Patients with suspected sepsis, that is, patients with a quick Sequential Organ Failure Assessment (qSOFA) score≥2 at the participating centers will be screened based on routine diagnostics and eligibility criteria and would consent to participate in the study. A low dropout rate is expected, due to short intervention time and fewer and brief follow-up periods. Nonetheless, participants will be informed about their right to withdraw from the study; and in the case of dropouts or withdrawal, the reasons will be documented. To achieve a sample size of 340 patients, a recruitment time of around 12-18 months is needed based on annually admission rate of 1000 patients and an expected recruitment rate of 5%-10% (50/1000-100/1000) per center. Multimedia Appendix 2 depicts the template for an attrition diagram [32]).

To ensure adherence, a standardized protocol and a checklist for the intervention will be provided to the participating centers and followed for each participant by the study investigators. The study investigators will document the patient's further treatment and monitor the treating department staff, to ensure that the protocol and necessary variables are documented. Patients or relatives will be reminded at the time of discharge from the hospital that they will be contacted for a follow-up.

### Eligibility Criteria

The eligibility criteria for patient recruitment is shown in Textbox 1.

Inclusion and exclusion criteria for patient recruitment.Inclusion Criteria:Admitted into the emergency department.Age 18-65 years.Sepsis with a quick Sequential Organ Failure Assessment (qSOFA) score≥2 [3,14,28,33]Consent by the patient or legal guardian.Exclusion Criteria:Mechanical ventilation at screening.Unconsciousness when admitted to emergency department (with Glasgow Coma Scale score<8)Preexisting pulmonary pathology as assessed by clinical symptoms or radiographic evidence in chest x-ray or by pulmonary bedside ultrasound (>2 B lines, a comet-tail artifact)History of pulmonary disorders (chronic obstructive pulmonary disease, asthma, parenchymal lung disease, or edema) or procedures.Preexisting cardiac pathology, disease, or dysfunction (ejection fraction<50, New York Health Association class>2) lung, or cardiac surgical procedures.History of liver cirrhosis, cancer, autoimmune disease, or immunosuppression.Patients under palliative care and patients facing imminent and inevitable death in the next 30 days due to causes other than sepsisSevere burns.Advanced kidney disease (chronic kidney disease stage 4 or above)Unstable medical conditions (eg, uncontrolled diabetes, uncompensated cardiac issues, heart failure, or chronic obstructive pulmonary disease).PregnancyWith other reasons or diseases needing a restricted fluid administration

### Randomization and Blinding

Randomization will be web-based across centers using simple randomization stratified for patient’s age and center, with 1:1 allocation. The sequence will be confidential and will be managed by a researcher independent of patient treatment. The treating physician will use the web-based randomization service—Viedoc (PCG Solutions AB). To increase the internal validity, possible confounders, such as pulmonary disorders, mechanical ventilation affecting imaging findings and bias results, kidney disease, and pre-existing cardiac disorders will be excluded by strictly implementing the eligibility criteria (Figure 1, Textbox 1, and Multimedia Appendix 2).

Patients and physicians will be unblinded to avoid endangering the patient's health and life in the situation of an emergency. However other study investigators collecting data, drawing blood samples for the analysis of PaO_2_/FiO_2_ and other parameters, and documenting, entering, or analyzing data will be blinded. Allocation concealment will be maintained until all data is collected and analyzed for the blinded personnel. The treating physician and patients will be instructed not to disclose information to the independent assessor and the data analyst. All breaches of blinding will need to be reported and documented.

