### Sample Size Justification

The sample size considerations were based on the PaO_2_/FiO_2_ differences between groups obtained from comparable prospective studies [26,39,40], where EVLW indices were used as a predictor for mortality. A PaO_2_/FiO_2_ ratio difference (delta) of 48 mm Hg was detected between the groups of survivors (mean 150, SD 81) and nonsurvivors (mean 198, SD78). Based on these studies, a delta of 25 mm Hg between the groups was considered clinically meaningful and feasible for our study. Interim analysis for safety reasons will be performed after 50% (170/ 340) of patient recruitment. An independent blinded statistician would perform the interim analysis and report to the data safety monitoring committee, as only safety is the monitored outcome no alpha level modification is needed (Multimedia Appendix 4 Interim analysis and safety).

The sample size was calculated (*α*=.05; ß=.80) with a potential dropout rate of 5% (17/340), resulting in n=170 patients per arm in a total of N=340 patients (Figure 1).

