### Statistical Analysis

The primary outcome will be PaO_2_/FiO_2_, a continuous variable. Mean (SD) will be reported after testing for normality, and then will be analyzed via *t* test. For secondary outcomes, a repeated measure ANOVA and *t* test will be used for analysis of continuous data. Categorical data will be reported using proportions and will be analyzed using chi-square test.

All analysis will be conducted according to the principle of intention-to-treat, and multiple imputation technique will be used to account for missing data. A subgroup analysis will be performed based on randomization of age, site, and severity of sepsis. An intention-to-treat analysis approach will be used in this study (Multimedia Appendix 4 Missing Data).

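### Simple randomisation within age and centre strata does not enforce the balance that the stratification is meant to give

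*Protocol article*

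**What the plan says.** Under Randomization and Blinding, the protocol article describes web-based allocation "using simple randomization stratified for patient’s age and center, with 1:1 allocation". It names two factors, age and centre. Neither that section nor any other mentions blocks, minimisation or another restriction.

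Under Statistical Analysis, the primary outcome is handled as follows: "Mean (SD) will be reported after testing for normality, and then will be analyzed via *t* test". No stratification factor is mentioned there. The same section adds: "A subgroup analysis will be performed based on randomization of age, site, and severity of sepsis". Read literally, this attaches randomisation to three factors, one of which (severity) is absent from the allocation scheme.

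The Sample Size Justification gives the planning difference ("a delta of 25 mm Hg between the groups was considered clinically meaningful and feasible for our study") and the size, "resulting in n=170 patients per arm in a total of N=340 patients". The numbers of centres and of age groups are not given.

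**The concern.** Stratifying means keeping the arms close to equal within each age-by-centre cell. That needs a restriction inside each cell, such as permuted blocks, or a minimisation rule. Simple randomisation is by definition unrestricted. The sentence therefore names two balancing factors and a method that balances neither. If a restricted scheme was intended, the published method is misnamed. If simple randomisation was intended, the stratification has no effect.

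Centre is a sensible factor to balance. Under Intervention, control-arm fluid practice after the initial bolus is left to the treating physician and local protocols. Analyses by site and by age are planned, and their precision depends on how evenly each subgroup splits. The severity wording adds a smaller uncertainty: a reader cannot be sure whether the scheme has two factors or three.

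**Working it through.** **1. The plan's own figure.** Inputs from Sample Size Justification: difference 25 mm Hg; SDs 81 and 78, average 79.5; alpha 0.05, taken as two-sided; power 0.80 (the printed beta of .80 is read as power); dropout 5%.

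n per arm = 2 × (1.960 + 0.842)² × 79.5² / 25² = 158.7, so 159. With dropout, 159 / 0.95 = 167.4, so 168. The plan states 170, so the figure reproduces to within 3%. Nothing below changes it.

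**2. Equivalence of the two schemes.** Under simple 1:1 randomisation each assignment is an independent draw with probability 0.5, whatever the patient's stratum. The joint distribution of all assignments is therefore the same whether the draws come from one list or from a separate list per stratum.

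**3. Overall imbalance, N = 340.** The arm difference has SD √340 = 18.4. From the exact binomial:
- P(difference ≥ 20) = 2 × P(X ≤ 160) = 0.303
- P(difference ≥ 36, that is 152:188 or worse) = 0.058
- the 95th percentile of the absolute difference is about 36.

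**4. Imbalance within strata.** The number of strata is an assumption. Recruitment and Adherence expects 50 to 100 patients per centre per year over 12 to 18 months, so 50 to 150 per centre. Then 340 / 150 = 2.3 and 340 / 50 = 6.8, which suggests 3 to 7 centres. With two age groups (also assumed), that gives 6, 10 or 14 strata. Under simple randomisation the mean absolute difference is approximately √(2n/π), with n the stratum size. Simulation of both list types agrees:

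| Strata (assumed) | Mean stratum size | One list | Separate simple lists | Blocks of 4 |
|---|---|---|---|---|
| 6 | 56.7 | 6.0 | 6.0 | 0.67 |
| 10 | 34 | 4.6 | 4.6 | 0.67 |
| 14 | 24.3 | 3.9 | 3.9 | 0.67 |

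The block size of 4 is illustrative. Its value follows from the unfinished last block: with 0, 1, 2 or 3 patients in it, equally likely, the mean difference is (0 + 1 + 2/3 + 1) / 4 = 0.67. With blocks in strata, the 95th percentile of the overall arm difference falls from 36 to between 4 and 6.

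For one stratum of 34 (5 centres × 2 age groups), P(13:21 or worse) = 0.23, and the central 95% range runs from 11:23 to 23:11. For one centre of 68 (340 / 5), P(27:41 or worse) = 0.11.

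**5. Effect on precision.** Efficiency relative to an equal split is 4 × n1 × n2 / N².
- Whole trial at 152:188: 4 × 152 × 188 / 340² = 0.989, so the standard error rises by about 0.6%. At 170:170 the standard error is 79.5 × √(2/170) = 8.62 and power is Φ(25/8.62 − 1.96) = 82.6%. At 152:188 it is 8.67 and power is 82.2%. The loss is about 0.4 points.
- One centre at 27:41: 4 × 27 × 41 / 68² = 0.958, so that centre's standard error rises by about 2%.

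**6. Factor lists side by side.** Randomization and Blinding: age, centre. Statistical Analysis: age, site, severity. Nothing elsewhere in the article puts severity into the allocation scheme.

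**The case against.** The best defence is that *simple* is loose wording. Naming age and centre shows an intent to balance, and the article defers further details to the registered protocol. That is plausible, and the absence of block sizes is not a finding. It does not rescue the sentence, because the article positively names a method that contradicts the intent.

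A second defence is that simple randomisation is valid and the least predictable choice. This stands. Predictability matters here, since the treating physician is unblinded and operates the web service.

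Three stronger readings are tempting and should be resisted:
- A reader might infer that the trial result would be biased or underpowered. It would not be. Allocation remains random, arms are balanced in expectation within every centre, the t test holds its error rate, and the power loss is negligible even at 152:188.
- A reader might infer that ultrasound skill and the FiO2 approximation will differ by site, making centre imbalance serious. The article does not establish this. It requires a common workshop, at least 20 validated scans per operator, quality monitoring and inter-rater checks, and it refers to generally accepted FiO2 values with no sign of site-specific conventions. Only discretionary fluid practice is supported as a source of site variation.
- A reader might infer that severity is a planned but omitted stratum. The sentence is ambiguous and may simply list the subgroups. Randomization and Blinding is the operative text and is clear about its two factors.

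**Conclusion.** The point holds as a wrongly stated method. As written, stratification by age and centre does not enforce balance on either. The cost is chance imbalance: probability 0.30 of an overall difference of 20 or more, and mean within-stratum differences of roughly 4 to 6 patients where blocking would leave under one. Site and age subgroup analyses are somewhat weaker as a result. The overall figures rest only on N = 340 and 1:1 allocation. The stratum figures rest on an assumed 3 to 7 centres, two age groups and equal expected stratum sizes. Validity, the primary test and the sample size are untouched, so this is a low-to-moderate point. The severity sentence is a secondary matter of wording.

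**What to change.** - **Randomization and Blinding:** replace *simple* with the restricted method to be used within centre-by-age strata, and configure the web service to match. Examples are permuted blocks of randomly varying size not disclosed to sites, or minimisation on centre and age with a random element.
- **Statistical Analysis, primary outcome:** adjust for age and centre, for example with a linear model containing treatment, age group and centre. After restricted allocation, a t test that ignores the strata tends to be conservative.
- **Statistical Analysis, subgroups:** describe age and centre as the randomisation strata and severity as a subgroup defined at baseline.

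The cost is one system setting and three short text changes, with no change to the sample size. The downside is slightly more predictable allocation in an open-label trial, which varying, undisclosed block sizes or a random element keep small. The Results section describes funding, ethical approval and centre selection as still in progress, so on the article's account this can be done before enrolment.
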